## Abstract

**Background:**

Radiation Therapy (RT) is a common treatment after breast cancer surgery and a complex process using high energy X-rays to eradicate cancer cells, important in reducing the risk of local recurrence. The high-tech environment and unfamiliar nature of RT can affect the patient’s experience of the treatment. Misconceptions or lack of knowledge about RT processes can increase levels of anxiety and enhance feelings of being unprepared at the beginning of treatment. Moreover, the waiting time is often quite long. The primary aim of this study will be to evaluate whether a digital information tool with VR-technology and preparatory information can decrease distress as well as enhance the self-efficacy and health literacy of patients affected by breast cancer before, during, and after RT. A secondary aim will be to explore whether the digital information tool increase patient flow while maintaining or increasing the quality of care.

**Method:**

The study is a prospective and longitudinal RCT study with an Action Research participatory design approach including mixed-methods data collection, i.e., standardised instruments, qualitative interviews (face-to-face and telephone) with a phenomenological hermeneutical approach, diaries, observations, and time measurements, and scheduled to take place from autumn 2020 to spring 2022. The intervention group (n = 80), will receive standard care and information (oral and written) and the digital information tool; and the control group (n = 80), will receive standard care and information (oral and written). Study recruitment and randomisation will be completed at two centres in the west of Sweden.

**Discussion:**

Research in this area is scarce and, to our knowledge, only few previous studies examine VR as a tool for increasing preparedness for patients with breast cancer about to undergo RT that also includes follow-ups six months after completed treatment. The participatory approach and design will safeguard the possibilities to capture the patient perspective throughout the development process, and the RCT design supports high research quality. Digitalisation brings new possibilities to provide safe, person-centred information that also displays a realistic picture of RT treatment and its contexts. The planned study will generate generalisable knowledge of relevance in similar health care contexts.

*Trial registration*: ClinicalTrials.gov Identifier: NCT04394325. Registered May 19, 2020. Prospectively registered.

## Background

Among women, breast cancer is the most diagnosed cancer and the leading cause of cancer death worldwide [1]. In 2019, the Swedish national cancer register recorded 9225 cases of breast cancer; 9157 women and 68 men (0.7%). The incidence rate of breast cancer in Sweden is expected to continue to rise, due to an increase in both the general and ageing population numbers [2]. Radiation Therapy (RT) is a common treatment (received by 75–80% of breast cancer patients) after surgery and is a complex process based on the use of high energy X-rays to eradicate cancer cells, important in reducing the risk of local recurrence [1]. While the RT procedure itself takes only a few minutes and is painless, it requires meticulous preparation and patients then need to attend the RT treatment centre 5 days a week for up to 3–5 weeks. Moreover, in Sweden, the waiting time is often quite long, sometimes up to 10 weeks [2]. The high-tech environment and unfamiliar nature of RT can affect the patient’s experience of the treatment [3–5]. Furthermore, misconceptions or a lack of knowledge about RT processes can increase their levels of anxiety and enhance feelings of being unprepared at the beginning of treatment [6–8].

Having received correct information about future treatment may enable patients to realistically assess advantages and disadvantages as well as foresee possible treatment results. This may in turn create a feeling of increased knowledge and security as well as reduce distress for the patient [9–13]. A number of Swedish acts state that the healthcare system must provide each patient with individually tailored information and the opportunity to choose between different treatments [14–16] or stipulate that healthcare providers should actively ensure that the information has been received and understood by the patient [10]. Having a person-centred approach to information provision and communication means to enhance shared decision making, seeing the person as a capable individual who wants to adapt generic information to his or her social context and experiences [17, 18].

When informing patients, their health literacy must also be considered, i.e., their ability to acquire, understand, and use information about their health, including that related to cognitive and social functions [19]. Health literacy can be seen as being dynamic, and hence can fluctuate, depending on the state of the individual, the situation, the culture, or the environment [20].

Self-efficacy, referring to a persons’ belief in his/her ability to deal with specific situations [21] such as in this case a cancer diagnosis, treatments, and transitioning to survivorship [22]. Cancer patients’ perceived self‐efficacy may directly or indirectly affect health behaviours, lifestyle adjustments and psychological growth, psychological distress, and physical outcomes, as well as quality of life (QoL) [23, 24]. Psychosocial distress may appear early in the diagnostic process and can have negative effects on compliance with treatment and subsequent quality of life [22].

There is a need for new ways to inform and involve patients, hence there is a strong call for digitalized tools to be used in healthcare. To be effective, however, digital tools must be developed based on research that also follows quality standards [25]. More and more, patients request they are provided information through videos, accessible for later review at home and for sharing with loved ones, as many patients travel substantial distances to receive care [26]. Furthermore, videos and audio-visual materials have proven to be successful communication tools and the format also supports the distribution and sharing of information with others [27–29]. Virtual reality (VR) has the inherent potential to be interactive because its content is generated in real time, not ahead of time, which makes the experience even more immersive [30]. Specifically, VR differs from other forms of media because it induces the sense of “presence”, i.e., the feeling of “being there” inside the virtual experience produced by the technology [31]. VR-interventions for cancer patients were investigated in a meta-analysis by Zeng et al. [32], showing its effects on improved learning through cognitive training and significantly decreased fatigue. A recent study indicated that a virtual reality education for breast cancer patients could improve RT knowledge and perhaps decrease anxiety as well as was appreciated by the patients [12]. Moreover, virtual reality radiotherapy educational program could have a positive effect on patients prior to their initial RT session by providing them with useful content and decreasing their anxiety about the process, thus increasing the patient RT comprehension [33].

In another study, the majority (86%) of the participants considered that the information they received did not provide them with an adequate understanding of the treatment and what it entailed [34]. Participants identified potential benefits of VR video viewing before the first day of treatment and felt that it could increase understanding of the treatment process, specifically the spatial and acoustic aspects of treatment. The authors concluded that a VR education tool has the potential to enhance standard patient education, increasing understanding of treatment and decreasing anxiety.

However, the potential outcomes related to Health Literacy are scarcely evaluated. Moreover, most studies were of relatively low methodological quality or pilot studies and the need for research of more robust study design and larger sample sizes has been identified.

The primary aim of this study will be to evaluate whether a digital information tool with VR-technology and preparatory information can decrease distress as well as enhance the self-efficacy and health literacy of patients affected by breast cancer before, during, and after RT. A secondary aim will be to explore whether the digital information tool increase patient flow while maintaining or increasing the quality of care.

## Methods

### Study design

The study (ClinicalTrials.gov Identifier: NCT04394325) is a prospective and longitudinal RCT study with an Action Research (AR) participatory design approach, including mixed-method data collection, i.e., standardised instruments, interviews (face-to-face and telephone), diaries, observation, and time measurements. To ensure transparency and rigour the CONSORT [35] checklist for randomised trials and COREQ [36] checklist for qualitive research will be applied. The timeline for the study is scheduled between autumn 2020 to spring 2022. The study will consist of two arms: (A) an intervention group (*n* = 80), who will receive standard care and information and the digital information tool; and (B) a control group (*n* = 80) who will receive standard care and information (oral and written). Recruitment and randomisation will be completed at two hospitals in the Western part of Sweden. Two nurses will act as research assistants at the respective hospitals.

### Sample

Adult patients (> 18 years) diagnosed with breast cancer, stage I–II, who are not receiving adjuvant or neo-adjuvant chemotherapy or anti-Her-2 treatment and with RT as additional treatment after surgery, will be consecutively included during the planned post-operative visit to the surgical clinic. They will also need the ability to read, write, and understand Swedish to adhere to the digital information tool and the data collection instruments, and have access to a smartphone or a tablet. Patients responding to these inclusion criteria will be consecutively asked to participate at the post-surgery follow-up visit and receive information (oral and written) about the study. After providing their signed informed consent, participants will be randomized to either the intervention group (A) or the control group (B) by drawing a note (marked with group A or B) for each participant from a black box. Randomization will be stratified by hospital, and a total of 80 participants will be finally included at each hospital (40 in each group). The participants in the intervention group will receive oral and written information regarding the digital information tool.

#### Sample size and hypothesis

The Distress Thermometer will be used as the primary outcome measure and used as a basis for the power calculation. A sample size of 63 persons in each group (a total of *n* = 126) would give an 85% power to detect a 0.10 improvement in the intervention group at an alpha = 0.05.

The null hypothesis is that there is no difference in distress between the intervention group and the control group; the alternative hypothesis is that the intervention group will experience 10% lower distress than the control group at the follow-up, six months post-completion of RT. The anticipated recruitment rate is 4.4 participants per site and month.

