#### Primary outcome measure

*DIS-A. The NCCN Distress Thermometer* is a brief screening tool for cancer patients to assess psychosocial distress [39], including 34 dichotomous items on the presence of physical, emotional, family, practical, and spiritual problems. A score of 4.5 or higher indicates the patient is distressed and in need of support. The Swedish translation of the DT/PL is consistent with the original English version [40].

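### The 85% power for a 0.10 improvement cannot be reproduced: 63 per group detects about 0.54 SD, and 0.10 has no unit and is not reconciled with 10% lower distress

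*Protocol article*

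**What the plan says.** The section on sample size and hypothesis in the protocol article makes the Distress Thermometer the basis of the calculation: "The Distress Thermometer will be used as the primary outcome measure and used as a basis for the power calculation". It then gives the number, "A sample size of 63 persons in each group" (126 in total), and says that this "would give an 85% power to detect a 0.10 improvement in the intervention group", with alpha 0.05.

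The next paragraph of that section puts the target in other terms: "the intervention group will experience 10% lower distress than the control group at the follow-up, six months post-completion of RT".

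The section on the primary outcome measure describes 34 yes/no items and a cut-off: "A score of 4.5 or higher indicates the patient is distressed and in need of support". It does not say which quantity the calculation used (mean score, number of problems, or share of patients above the cut-off), and it gives no score range. The abstract, the study design section and the sample section plan 80 per group, 160 in all.

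**The concern.** The article prints the sample size, power, alpha and effect, so the reader is invited to check them. The effect appears twice in forms that are not obviously the same quantity. The first is an improvement of 0.10 without a unit. The second is a percentage that, read plainly, is relative to the control group. No SD, control mean or control rate converts one into the other.

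This is the only power statement for the primary outcome. If 0.10 is read as a standardised effect, as a difference in proportions, or as a relative fall in the mean at ordinary spreads, the trial has far less than 85% power for it. A null result could then be taken as evidence against a 10% reduction that the trial had little chance of detecting.

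**Working it through.** **Inputs from the article.** 63 per group for the calculation; 80 per group planned; power 85%; alpha 0.05; effect 0.10 or 10%; comparison between groups at six months. Sidedness is not stated; two-sided is assumed, and one-sided is also shown for the detectable difference.

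**Inputs not in the article.** SD, control mean, control rate and score range. Values used for these below are assumptions, shown as ranges.

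**Step 1: reproduce the stated figure.** This cannot be done from the article, because a unit and an SD (or a control rate) are needed. What can be computed is the standardised difference that the design detects.

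**Step 2: detectable difference.** By the normal approximation, d = (z₀.₉₇₅ + z₀.₈₅) × √(2/n).
- n = 63: (1.960 + 1.036) × √(2/63) = 0.534; the t-test gives 0.538.
- n = 80: (1.960 + 1.036) × √(2/80) = 0.474; the t-test gives 0.477.
- One-sided, n = 63: 0.480 by the t-test.

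**Step 3: the SD that would make the claim true.** A difference of 0.10 equals 0.538 SD when the SD is 0.10 / 0.538 = 0.186 in the same unit.

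**Step 4: power under each reading, 63 per group, two-sided 0.05.**

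| Reading of the target | Assumption | Power |
|---|---|---|
| 0.10 SD | none | 8.6% (9.6% with 80 per group) |
| 10 percentage points | 20% vs 10% | 35% |
| 10 percentage points | 30% vs 20% | 25% |
| 10 percentage points | 50% vs 40% | 20% |
| 10% relative fall in the mean | mean 3, SD 3 (0.3/3 = 0.10 SD) | 9% |
| 10% relative fall in the mean | mean 4, SD 2 (0.4/2 = 0.20 SD) | 20% |
| 10% relative fall in the mean | mean 5, SD 2 (0.5/2 = 0.25 SD) | 29% |
| 10% of the scale: 1 point on an assumed 0–10 scale | SD 1.5 | 96% |
| same | SD 1.86 | 85% |
| same | SD 2 | 80% |
| same | SD 2.5 | 61% |
| same | SD 3 | 46% |

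Means are compared with the two-sample t-test or its normal approximation, which agree to about one percentage point. Proportions use the pooled two-sample normal test.

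**Step 5: sample size for the literal standardised reading.** 2 × ((1.960 + 1.036)/0.10)² = 1,796 per group (1,797 with the t-test).

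**Step 6: another possible origin of the 0.10.** A group-by-time interaction with Cohen's f = 0.10, three time points and an assumed correlation near 0.65 gives about 84% power with 126 patients. That may be where the figure came from, but it is a different hypothesis from the six-month group difference in the article.

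**The case against.** A reader might infer that the design delivers 85% power under no reading of its hypothesis, and that the true detectable effect of 0.54 SD contradicts the stated 0.10. The article does not support either inference. It never says that 0.10 is in SD units. If the SD is 0.186 in the unit of 0.10, then 0.10 and 0.54 SD are the same difference.

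Two readings can reach 85%. One is a 10% relative fall with a coefficient of variation of 0.186, which is a tight spread but is not excluded by anything in the text. The other takes both 0.10 and 10% as a tenth of the scale range. This has the merit of making the two statements agree, and on an assumed 0–10 scale with SD 2 it gives 80% with 63 per group and 88% with 80. So this is not a proven arithmetic error: inputs are missing, rather than a full set of inputs giving another answer.

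It can also be said that a condensed article may leave the SD, sidedness and dropout to the full protocol. That is fair, and their absence alone would not be a point. What remains is that the article prints an effect that cannot be interpreted, gives it a second time in a form not tied to the first, and attaches 85% power to it. The scale-range reading needs a meaning of 10% lower than the control group that the text does not give, and its power falls quickly as the SD rises.

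**Conclusion.** The power statement cannot be reproduced and should not be relied on as written. What is firm is that, at two-sided alpha 0.05, 63 evaluable patients per group have 85% power for about 0.54 SD, and 80 per group for about 0.48 SD. The stated claim is true only if the SD is about 0.186 in the unit of 0.10.

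On the standardised, percentage-point and relative-mean readings, power with 63 per group ranges from about 9% to 35%. Those ranges rest on assumed control rates of 20–50%, means of 3–5 and SDs of 2–3; only the 9% for a standardised effect of 0.10 needs no such assumption. On the scale-range reading it runs from 96% to 46% as the assumed SD goes from 1.5 to 3. The article does not allow a choice among these, so the conclusion is that the claim is ambiguous and conditional, not that it is false.

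**What to change.** Change the wording of the sample size and hypothesis section:

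- State what the design delivers: 85% power, two-sided alpha 0.05, for a difference of about 0.54 SD with 63 evaluable patients per group (about 0.48 SD if all 80 are evaluable).
- Keep the 10% hypothesis, but express it in Distress Thermometer units, with the assumed SD and control value and their source, and report the power that the design gives for that target.
- Say which variable is powered: the score, the problem items, or the proportion at or above 4.5.
- Reconcile 0.10 with 10% lower, so that one target is stated once and in one unit.

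No extra patients or data are needed. The cost is that the stated detectable effect may look less favourable than the present sentence suggests, and the power for the 10% target may turn out below 85%.

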### Data collection

Socio-demographic data concerning age, marital status, number of persons in household, level of education, working/retired/sick leave, stage of disease, co-morbidities, and treatment will be gathered from the patients and/or their medical charts. The instruments for data collection will be administrated in person or by post at the baseline collection, and by post (including a pre-paid return envelope) on consecutive collections (Table 1). Two reminders will be sent for each data collection, separated two weeks in time if necessary. Data will be coded and manually entered in SPSS. The SPSS database will be stored on a secure digital storage (JU share files) at Jönköping University.

**Table 1 Tab1:** Data collections at different points in time

Point in time	Data collections
Baseline	Socio-demographic and co-morbidity data Distress (DIS-A); Self-efficacy (GSES); Health literacy (functional, communicative & critical, e-HLQ) Notebook written by 30 patients
Week of commencing RT treatment	Distress (DIS-A) Notebook collected and returned after reading
Within a month of completion of RT treatment	In depth/or telephone interviews with participants
Six months post-completion of RT treatment	Distress (DIS-A); Self-efficacy (GSES); Health literacy (functional, communicative & critical, e-HLQ) Telephone interviews with participants

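### At the stated recruitment rate, enrolling 160 patients and following each to six months after RT needs about 25–28 months, but the stated study timeline gives at most about 21

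*Protocol article*

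**What the plan says.** The Study design section names two hospitals: "Recruitment and randomisation will be completed at two hospitals in the Western part of Sweden". The Sample section sets 80 participants at each, 160 in all, included at the post-operative visit to the surgical clinic. The section Sample size and hypothesis gives the pace: "The anticipated recruitment rate is 4.4 participants per site and month". It also bases 85% power on 63 patients per group, 126 in total.

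The same section fixes the time of the main comparison. Its alternative hypothesis is that "the intervention group will experience 10% lower distress than the control group at the follow-up, six months post-completion of RT". Table 1 under Data collection lists the matching questionnaire at "Six months post-completion of RT treatment".

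On the calendar, Study design says "The timeline for the study is scheduled between autumn 2020 to spring 2022". The Method paragraph of the Abstract describes the whole longitudinal trial as "scheduled to take place from autumn 2020 to spring 2022". Neither place separates the end of recruitment from the end of follow-up.

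The Background supplies the time between inclusion and the end of RT. RT takes up to 3–5 weeks, and "in Sweden, the waiting time is often quite long, sometimes up to 10 weeks".

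**The concern.** The rate, number of sites, sample size, endpoint time and study dates are all stated, so they can be checked against each other, and they conflict. This is not a detail left out by a condensed article. The last patients enrolled would have their six-month assessment due well after the stated end of the study.

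What is at stake is the number of patients with a primary outcome. If data collection really ended on the stated schedule, the most recently enrolled patients would have no six-month distress score. The number available could then fall below the 126 on which the power statement rests.

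**Working it through.** **Inputs from the article.** Two sites, 4.4 participants per site and month, 160 patients to enrol, 126 needed for the stated power, RT of 3 to 5 weeks, a wait of up to 10 weeks, and the main comparison 6 months after RT.

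**Assumptions added here.** The widest ordinary reading of the dates is 1 September 2020 to 31 May 2022, or 21 months. Narrower readings of the seasons give as little as about 16 months. Both sites recruit at the full rate from the first day. One week is 7 × 12 / 365.25 = 0.230 months.

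**1. The stated rate.** 80 patients per site / 18 months = 4.44, which rounds to the stated 4.4. The rate is therefore what about 18 months of recruitment would require.

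**2. Time to enrol.** 160 / (2 × 4.4) = 160 / 8.8 = 18.2 months.

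**3. Time from inclusion to the six-month comparison.**
- No wait, 3 weeks of RT: 6 + 3 × 0.230 = 6.7 months.
- 10-week wait, 5 weeks of RT: 6 + 15 × 0.230 = 9.45, about 9.5 months.

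**4. Total time needed for 160 patients.**
- Shortest: 18.2 + 6.7 = 24.9 months.
- Longest: 18.2 + 9.45 = 27.6 months.

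In a 21-month window, 21 − 18.2 = 2.8 months remain after the last enrolment, against at least 6.7 needed. Even with wait and RT counted as zero, 18.2 + 6 = 24.2 months exceeds 21.

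**5. Patients reaching the endpoint if collection stopped at the end of the window.** The number is 8.8 × (window − time to endpoint), before any loss to follow-up.

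| Window (months) | No wait, 3 weeks RT | 10-week wait, 5 weeks RT |
|---|---|---|
| 21 | 125.9 | 101.6 |
| 18 | 99.5 | 75.2 |
| 16 | 81.9 | 57.6 |

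**6. Power.** The 126 cannot be reproduced, because no SD, base rate or sidedness is given. Taking 85% at 63 per group as given, and assuming a two-sided comparison of means at 0.05, the implied standardised effect is (1.960 + 1.036) × √(2/63) = 0.534. With 101 evaluable (50.5 per group), 0.534 × √(50.5/2) − 1.960 = 0.72, a power of about 77%. With 75 evaluable it would be about 64%.

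**The case against.** The strongest reply is that the harm is hypothetical. No section sets a data cut or closes follow-up in spring 2022. Inclusion is fixed by number at each hospital, not by date. Table 1 schedules the six-month questionnaire without exception, and two reminders are planned for each collection. Because the stated rate matches 18 months of enrolment, the dates may have been meant as the recruitment period. All of this stands as a limit on the consequence. It does not remove the conflict, since both places that give the dates attach them to the study as a whole. If only recruitment was meant, the wording still needs correcting.

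Four stronger readings are tempting, and the article does not support them:

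- *Recruitment fills the whole timeline.* In a 21-month window, 18.2 months leaves 2.8.
- *The trial will certainly miss 126.* The most favourable case gives 125.9 before loss, practically the target. A window of about 22 months with no wait and 3 weeks of RT would exceed it: 8.8 × (22 − 6.69) = 134.7. A clear shortfall needs some waiting time, some loss to follow-up or a shorter window.
- *The 160 planned against 126 needed shows a 21% loss* (34 / 160), so the evaluable number should be cut by that much again. The article states no attrition rate and does not explain the difference.
- *Losing the last recruits biases the comparison.* Patients are randomised concurrently within hospital, so a calendar cut-off would fall on both arms. It costs power, and nothing in the article shows a bias between arms.

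The 9.5-month figure is also an extreme. The 10 weeks is a national upper value, not a wait reported for these two hospitals.

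**Conclusion.** The stated timeline is wrong as written. With the article's own rate, sample size and endpoint, the trial needs about 25 to 28 months, against at most about 21. That conclusion depends only on the reading of the seasons and on the dates covering the whole study, as the text says. The most generous reading of the seasons still falls about 4 months short.

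The effect on the evaluable number is conditional. Only if data collection ended on the stated schedule would about 102 to 126 patients reach the endpoint in a 21-month window, and fewer in a shorter one. That is at or below the 126 behind the stated 85% power. The 77% figure for about 101 evaluable patients also rests on the assumed two-sided comparison of means.

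**What to change.** In the Abstract (Method), Study design, and Sample size and hypothesis, replace the single timeline with two dates: end of recruitment, about spring 2022, and end of six-month follow-up, about autumn 2022 to early 2023. Say that follow-up continues until the last randomised patient's six-month questionnaire and its reminders are complete, and that the primary analysis comes after that.

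If spring 2022 is a fixed end for the whole study, restate the evaluable number that can be reached by then, and its power, with the assumptions given.

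The cost is wording and a longer period of postal follow-up, with no extra patients. The result comes about 4 to 9 months after the stated end: 24.9 − 21 = 3.9 months at the least, and 27.6 − 19 = 8.6 months if the window is taken as 19 months. The delay is longer if the stated window is read more narrowly still.
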